### Sample collection

For the PK analysis and second-generation gene sequencing, 5 ml blood samples will be collected into tubes containing ammonium heparinate and centrifuged immediately at 4000 g for 10 min to obtain plasma samples. These samples will be then transferred into polypropylene vials and kept at −20°C until analysis. For the 7.5 and 15 g dose groups, samples will be collected at dosing (time 0), and 15, 30, 45, 60, 90, 120, 150, 180, 240, 360, 480, 600, 720, 1440, 2160 and 2880 min.

Furthermore, a comprehensive set of biomaterials including EDTA-plasma (6 ml), serum (5 ml) and urine (6 ml) will be collected and stored for future laboratory analyses.

### Safety assessments

Safety and tolerability will be assessed subjectively and objectively. Subjective tolerability will be assessed by questioning subjects about any adverse events (AE). Objective tolerability will be assessed at scheduled intervals by vital signs (body temperature, heart rate and blood pressure), electrocardiograms (ECGs), the examination of intravenous infusion sites, and identification of adverse events (AEs). AE information will be collected throughout the study, based on spontaneous volunteer reports, interviews, clinical examinations and laboratory tests (hematology, serum biochemistry, and urinalysis). The investigators will assess all clinical AEs according to the Medical Dictionary for Regular Activities criteria, in terms of intensity (mild, moderate, or severe), duration, outcome and relationship to the study drug. Those which are life threatening, or lead to death, hospitalization, disability, or medical intervention to prevent permanent impairment or damage, will be considered as serious adverse events (SAE). Each adverse event occurring to a subject has to be recorded in the case-report form.

All study procedures are illustrated in Figure 1.

**Figure 1 Fig1:**
[figure not shown]
**Patient flowchart detailing the process, including screening, allocation, and analysis.**

### Instrumentation and conditions

The LC-MS/MS system consists of an ULTIMATE 3000 series UHPLC (Thermo Fisher Scientific, USA) coupled to a TSQ QUANTUM ACCESS MAX Mass Spectrometer (Thermo scientific, USA). Chromatographic separation will be performed on a Waters Acquity UPLC BEH C18 column [100 mm*2.1 mm (i.d.); 1.7μm] (Waters, USA). The standards and samples will be separated using a mobile phase consisting of 0.1% formic acid in water (solvent A) and methanol (solvent A). The gradient elution program will be: 0–1 min, 20% A; 1–8 min, 20-100% A; 8–12 min, 100% A; and then back to 20% A to recondition the column for 4 min. The flow rate of the mobile phase will be 0.3 ml/min, with the column temperature maintained at 40°C. ESI ionization performed in the positive ion mode with a spray voltage of 3,000 V and negative mode with a spray voltage of 2500 V will be used. Sheath gas pressure and aux gas pressure will be set at 35 psi and 5 psi, respectively. A capillary temperature of 350°C will be used. Quantification will be performed in the multiple reaction monitoring (MRM) mode. The optimized parameters, such as collision energy (CE) and the tube lens for each compound, are summarized in Table 4. Xcalibur (Ver. 2.1; Thermo scientific, USA) is used to control the UHPLC/TSQ Quantum system, and to acquire and process data.

**Table 4 Tab4:** **Multiple reaction monitoring (MRM) transitions for quantification of the nine target compounds**

**Compound abbreviations***	**Monitoring Mode**	**Parent (m/z)**	**Product (m/z)**	**Tube lens (V)**	**Collision energy (eV)**	**Retention times (min)**
CCS	[M + H]+	285.16	270.30	99	23	6.43
CCSG	[M + H]+	447.24	285.30	98	20	4.89
FAN	[M + H]+	623.44	381.40	130	40	4.89
PAL	[M + H]+	352.23	336.30	89	29	5.44
5-O-M	[M + H]+	453.27	291.30	108	22	6.01
ONO	[M + H]+	431.25	269.30	97	17	6.00
FOR	[M + H]+	269.20	197.30	97	34	7.32
AST-IV	[M + Na]+	807.53	627.40	221	49	8.69
BER	[M + H]+	336.19	320.28	94	30	5.38

*The compound abbreviations and their associated terms:

AST-IV: astragaloside IV; BER: berberine; CCS: calycosin; CCSG: calycosin-7-O-β-D- glucoside; FAN: fangchinoline; FOR: formononetin; ONO: ononin; PAL: palmatine; 5-O-M: 5-O-methylvisammioside.

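### In Table 4 the 5-O-M transition coincides in mass and retention time with the predicted sodium adduct of ononin, so the 5-O-M channel may carry some ononin signal

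*Protocol article*

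**What the plan says.** The Instrumentation and conditions section describes an LC-MS/MS system with a "TSQ QUANTUM ACCESS MAX Mass Spectrometer" and states: "Quantification will be performed in the multiple reaction monitoring (MRM) mode". It gives no mass resolution. Table 4, titled "Multiple reaction monitoring (MRM) transitions for quantification of the nine target compounds", then fixes one transition and one retention time for each compound. Three rows matter here (compound, ion, precursor m/z, product m/z, tube lens, collision energy, retention time):

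- "5-O-M [M + H]+ 453.27 291.30 108 22 6.01"
- "ONO [M + H]+ 431.25 269.30 97 17 6.00"
- "AST-IV [M + Na]+ 807.53 627.40 221 49 8.69"

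5-O-M and ononin (ONO) are thus treated as separate analytes with separate channels. Astragaloside IV (AST-IV) is quantified as a sodium adduct.

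The Discussion describes the pre-trial human plasma method as selective. It announces 15 constituents and names 14, and 5-O-M is not among those named. Table 5 reports rat pharmacokinetics for six compounds, including ONO and 5-O-M.

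**The concern.** A tandem mass spectrometer tells analytes apart by precursor mass, product mass and retention time. For ononin carrying sodium instead of a proton, all three nearly equal the 5-O-M values. The AST-IV row shows that sodium adducts can form under these conditions, so the mechanism is plausible.

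The stake is the comparison of constitutional types. The plan applies noncompartmental analysis and PopPK modelling to the pill's constituents. If part of the 5-O-M reading is ononin, a difference between constitutional types in ononin exposure could reappear as a seemingly independent difference in 5-O-M, and the 5-O-M AUC, CL/F and V/F would be distorted to that extent. The three dose groups would not expose the problem: both compounds come from the same pill, so a false signal would rise with dose as a true one does.

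**Working it through.** **Inputs.** Transitions and retention times are from Table 4 and rat means (n = 6) from Table 5. The mass shift from a protonated to a sodiated ion is a physical constant, not in the documents: 22.990 - 1.008 = 21.982. Unit resolution, meaning a window of about 0.7 m/z, is assumed.

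**Step 1: predicted sodium adduct of ononin.**

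| | Ononin + Na, predicted | 5-O-M, Table 4 | Gap |
|---|---|---|---|
| Precursor | 431.25 + 21.98 = 453.23 | 453.27 | 0.04 |
| Product | 269.30 + 21.98 = 291.28 | 291.30 | 0.02 |
| Retention (min) | 6.00 | 6.01 | 0.01 (0.6 s) |

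The mass lost between precursor and product is 161.95 for ononin (431.25 - 269.30) and 161.97 for 5-O-M (453.27 - 291.30). The predicted product assumes that the sodiated ion loses the same piece as the protonated one.

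**Step 2: can the mass filter separate them?** The table's own spread is larger than these gaps. The calycosin ion appears as 285.30 when it is the product of its glucoside (CCSG) and as 285.16 when it is the precursor (CCS), a difference of 0.14. As a side check, the molecular formulas C22H22O9 (ononin) and C22H28O10 (5-O-M), which the documents do not give, yield exact masses of 453.116 and 453.176 for the precursors. The gap is 0.060, so separation needs a resolving power of about 453.18 / 0.060, or roughly 7,600. A unit-resolution quadrupole does not reach that.

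**Step 3: is the pair unusual?** All pairs in Table 4 were screened for a precursor match under the sodium shift, within 0.7 m/z. ONO and 5-O-M are the only hit.

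**Step 4: possible size, if Table 5 used these transitions.** Let k be the apparent 5-O-M concentration read per unit of ononin concentration. The false share of Cmax is k x 2.45 / 0.14 = 17.5k. The false share of AUC_last is k x 4.17 / 1.13 = 3.69k.

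| k | Share of mean 5-O-M Cmax | Share of mean 5-O-M AUC_last |
|---|---|---|
| 1% | 18% | 4% |
| 2% | 35% | 7% |
| 5% | 88% | 18% |
| 5.7% | 100% | 21% |

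The last row is the ceiling on means: k = 0.14 / 2.45 = 0.057 makes the whole mean peak ononin. At that k the share of AUC_tot is 0.057 x 4.89 / 2.31 = 12%.

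**Step 5: was the rat 5-O-M signal wholly ononin?** If it were, and calibration were proportional, the 5-O-M/ONO ratio would be the same for every exposure measure and the half-lives would agree. The ratios are 0.14 / 2.45 = 0.057 (Cmax), 1.13 / 4.17 = 0.27 (AUC_last) and 2.31 / 4.89 = 0.47 (AUC_tot). The half-lives are 7.04 h (ONO) and 42.79 h (5-O-M), a ratio of 6.1. The signal was not wholly ononin.

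**The case against.** The strongest reply is that a coincidence of masses is not an interference. The effect needs two facts that the documents do not give: how much ononin ionises with sodium, and whether that ion yields m/z 291 at the 5-O-M settings. AST-IV shows only that AST-IV forms a usable adduct. It is read at a tube lens of 221 V and 49 eV, against 108 V and 22 eV for 5-O-M, and Table 4 monitors ononin in its protonated form. This stands: the point is a risk, not a demonstrated error.

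A reader might infer that the two analytes are not separately measured, or that the 5-O-M results will be invalid. The documents do not support either. The mechanism runs one way only, since nothing in it puts 5-O-M signal into the 431.25 -> 269.30 channel, and Step 5 argues against a channel dominated by ononin. The shared rat Tmax of 0.25 h is weak evidence of cross-reading, because four of the six compounds in Table 5 have a mean Tmax between 0.22 and 0.25 h.

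The rat percentages may also not transfer. Table 5 includes two compounds (SEA and SEI) that are absent from Table 4, and the document does not say that the two tables share transitions. This stands too, so the percentages are illustrative.

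A reader might extend the point to palmatine and berberine, because the palmatine product (336.30) is close to the berberine precursor (336.19) and the retention times are 5.44 and 5.38 min. That is a different mechanism: palmatine would have to fragment in the ion source and the fragment would then have to yield 320.28. Nothing in the documents supports either step.

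Finally, selectivity testing is ordinary validation work that an article may leave to other records. That does not dispose of the point. Table 4 itself fixes the transition and the retention times, and the statement that the plasma method was selective does not name 5-O-M. With 14 names for 15 constituents, its coverage of 5-O-M cannot be confirmed.

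**Conclusion.** The point holds as a specific, unaddressed selectivity risk for one of the nine target compounds. As Table 4 stands, retention time does not separate 5-O-M from sodiated ononin, and mass does not either if the instrument runs at unit resolution. Ononin itself is still measured.

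The size is unknown. On the rat means, and only if those data came from these transitions, the plausible range runs from a minor to a complete contribution to the mean 5-O-M peak (18% to 100% for k of 1% to 5.7%), with a much smaller contribution to AUC_last (4% to 21%). The ceiling rests on means with wide SDs (Cmax 2.45 ± 1.51 and 0.14 ± 0.07 ng/ml), so it is approximate. Any distortion would fall mainly on Cmax and the early part of the curve.

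**What to change.** Before trial samples are run, inject ononin alone in blank plasma at the top of its calibration range and read the 453.27 -> 291.30 channel. A mixed standard will not do, because it contains the 5-O-M that the channel is meant to read. Compare the response with that of the lowest 5-O-M calibrator.

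- If it is negligible (for example below 20% of that calibrator), record the result; Table 4 can stay as it is.
- If not, change the gradient so that the two peaks separate, or quantify 5-O-M on a product ion that sodiated ononin does not give, and revise Table 4.
- If neither works, leave 5-O-M out of the comparison of constitutional types.

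A single-compound injection of palmatine read in the berberine channel may be added as an optional check.

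The cost is one or two injections of standards already needed for calibration. The downside is a slightly longer run or one fewer analyte. Finding the problem after the samples have been run could mean reanalysing them.

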### Analytical assays

Plasma concentrations and urinary excretion rates of the Qishe pill will be determined for up to 48 h using high-performance liquid chromatography with fluorometric detection according to a method used previously [20].

For sample preparation, plasma samples (100 ml) will be mixed with 100 ml of internal standard (diphenhydramine, purchased from the National Institutes for Food and Drug Control, Beijing, China) working solution. The samples will be extracted with 11:1 methanol–water (600 ml) by vortex-mixing for 1 min at high speed and centrifugation at 12,000xg for 10 min; 20 ml supernatant will be injected in the LC/MS/MS system for analysis.

### Pharmacokinetic parameters

The pharmacokinetic parameters of the Qishe pill will be estimated using noncompartmental methods. The actual blood sampling time will be used, and the maximum plasma concentration (*C*_max_) and time to maximum concentration (*T*_max_) will be recorded. The area under the plasma concentration-time curve (*AUC*) will be calculated using the linear trapezoidal rule. The elimination rate constant (*k*_e_ ) will be estimated from the least-squares regression slope of the terminal plasma concentration. The *AUC* from 0 to infinity (*AUC*_0−∞_) will be calculated by (*AUC*_0→t_ + *C*_t_ /*k*_e_ ) (*C*_t_ is the last plasma concentration measured). The elimination half-life (t_1/2_) will be calculated as ln 2/*k*_e_. The distribution volume (DF) will be calculated by Dose/*AUC*/*k*_e_.

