### Drug administration

Thirty-six healthy adult subjects in each cohort will be randomly divided into three groups to receive three different doses (low, 3.75 g; middle, 7.5 g; or high, 15 g). Subjects will be randomly assigned following simple randomization procedures (computerized random numbers) to each subgroup. Each dose of the Qishe pill (Shanghai Sundise Traditional Chinese Medicine Co., Ltd, China) with the same lot number will be administered orally with water (240 ml) after at least 10-hour fast. The low dose (3.75 mg) was calculated according to the applicable regulatory guidance [18,19], using the No Observable Adverse Effect Level (NOAEL) in the most sensitive species (500 mg/kg/day in Sprague–Dawley rats).

Subjects will be admitted to the study unit the evening before drug administration. On the day of administration, single doses of the Qishe pill will be taken orally, 1h after a standardized meal. Regular standardized meals will be provided 4 h after drug administration. Water is allowed as desired, except for 1 hour before and 2 hours after drug administration. The subjects will remain within a supervised investigational unit for the subsequent 3-d period for pharmacokinetic study and toxicity monitoring, providing 3-day blood and urine samples. Vital signs and clinical laboratory tests were done before and at 24 h after dosing. Furthermore, they will be requested to return to the study unit 4 d after drug administration for a follow-up visit.

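### The elimination constant is defined as a slope of concentration, with no log scale or sign, but is used in formulas that need a first-order rate constant; AUC to infinity also needs a rule for slow analytes

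*Protocol article*

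**What the plan says.** The Pharmacokinetic parameters section sets out a noncompartmental analysis. AUC is by the linear trapezoidal rule. The elimination rate constant ke "will be estimated from the least-squares regression slope of the terminal plasma concentration". Three quantities are then built on ke:

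- half-life, which "will be calculated as ln 2/*k*_e";
- AUC to infinity, the observed AUC plus Ct/ke, where Ct is the last measured concentration;
- volume: "The distribution volume (DF) will be calculated by Dose/*AUC*/*k*_e".

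The sampling period is described in three places. Drug administration keeps subjects in the unit for three days after dosing, "providing 3-day blood and urine samples", with a return visit at 4 days. Sample collection lists times for the 7.5 g and 15 g groups that end "480, 600, 720, 1440, 2160 and 2880 min". Analytical assays says plasma concentrations and urinary excretion rates "will be determined for up to 48 h".

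Table 4 includes formononetin (FOR) and 5-O-methylvisammioside (5-O-M) among its nine target compounds. Table 5, from six rats, is the only pharmacokinetic table in the article.

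**The concern.** A first-order elimination constant has units of 1/time and is minus the slope of ln(concentration) on time. The slope of concentration itself has units of concentration/time, is negative, and is proportional to the concentration level. Put into the article's formulas, it gives a half-life in time/concentration and an extrapolated area that is a time, not an area. The volume is in dose/concentration².

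The trial gives 3.75, 7.5 and 15 g. With linear kinetics and the same sampling times, a raw slope would differ fourfold between the lowest and highest dose with no difference in elimination. It would also change a thousandfold if results were reported in pg/ml instead of ng/ml.

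The second matter is separate. If an analyte's half-life is near 48 h, a correctly fitted ke is imprecise and much of AUC to infinity is extrapolated. A constitution comparison on AUC to infinity then depends heavily on a poorly estimated tail.

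**Working it through.** **1. The sampling window.** 2880 min / 60 = 48 h, which matches the assay statement. After 12 h the only points are 24, 36 and 48 h.

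**2. The ke rule taken literally.** This illustration assumes mono-exponential decline, a true half-life of 11.41 h (the rat AST-IV mean in Table 5) and terminal points at 24, 36 and 48 h. The true k is ln 2/11.41 = 0.06075 per h.

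With C0 = 1 ng/ml, concentrations are 0.2327, 0.1123 and 0.0542. For three equally spaced points the least-squares slope is (C48 − C24)/24 = (0.0542 − 0.2327)/24 = −0.00744. With C0 = 10 ng/ml it is −0.0744. The minus sign is dropped below so that the formulas can be evaluated at all.

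| Quantity | True | Literal, C0 = 1 | Literal, C0 = 10 |
|---|---|---|---|
| ln 2/ke | 11.41 | 93.2 | 9.3 |
| Ct/ke | 0.89 (C0 = 1); 8.91 (C0 = 10) | 7.28 | 7.28 |
| AUC to infinity / true (exact AUC to 48 h) | 1 | (16.46 − 0.89 + 7.28)/16.46 = 1.39 | (164.6 − 8.91 + 7.28)/164.6 = 0.99 |
| Volume / true (dose proportional to C0) | 1 | 5.9 | 0.82 |

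The literal Ct/ke does not change when every concentration rises tenfold, which shows that it is not an area. In pg/ml, the 93.2 becomes 0.093 for the same samples. With ke as minus the slope of ln(concentration), 11.41 h is recovered at either C0 and in either unit.

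**3. The window against Table 5 (rat means, n = 6).** The extrapolated share is (AUCtot − AUClast)/AUCtot, from group means.

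| Analyte | Half-life (h) | 48 h in half-lives | Extrapolated share |
|---|---|---|---|
| FOR | 51.24 ± 44.19 | 0.94 | (71.57 − 38.1)/71.57 = 46.8% |
| 5-O-M | 42.79 ± 16.29 | 1.12 | (2.31 − 1.13)/2.31 = 51.1% |
| ONO | 7.04 | 6.8 | (4.89 − 4.17)/4.89 = 14.7% |
| AST-IV | 11.41 | 4.2 | (129.75 − 107.74)/129.75 = 17.0% |

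These shares run to the rat study's last sampling time, which is not stated. If it was 12 h (assumed), carrying the tail on to 48 h at the mean half-life gives 46.8% × 2^(−36/51.24) = 29% for FOR and 51.1% × 2^(−36/42.79) = 29% for 5-O-M. If it was 24 h, the shares are 34% and 35%.

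**4. Precision of a correct log fit at these half-lives.** SE(ke)/ke = s/(√Sxx × ke), where s is the residual SD on the log scale. An assumed 10% residual CV gives s = 0.0998.

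- Points at 24, 36 and 48 h (Sxx = 288): 0.43 for FOR, 0.36 for 5-O-M.
- Adding the 12-h point (Sxx = 720): 0.27 and 0.23.
- For FOR with three points, the range over 5% to 20% CV is 0.22 to 0.86.

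**The case against.** The strongest reply is that the text never says untransformed. It calls ke a rate constant, and each formula that follows presupposes a log-linear fit, so the sentence is probably shorthand in a condensed article. That stands. A reader might infer that a raw-scale fit is planned and that the results will be wrong; the document does not show this. It shows an estimator stated incorrectly beside formulas it cannot feed.

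A reader might also join the two matters and conclude that the 48-h window biases ke. It does not: with a log fit and mono-exponential decline, the window costs precision and adds extrapolation, but no bias.

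Nor do the documents show that 48 h is too short in humans. The half-lives come from six rats, with an SD for FOR of 86% of the mean (44.19/51.24). No human half-life is given, and the human pilot curves in Figure 3 are not available here. It is tempting to say that 52% of FOR and 46% of 5-O-M exposure lies beyond 48 h, from 2^(−48/half-life). That assumes mono-exponential decline from time 0, which Table 5 contradicts. Cmax × half-life/ln 2 would be 694 h·ng/ml for FOR against a reported 71.57, and 8.6 against 2.31 for 5-O-M.

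Two further points stand in part. The NONMEM analysis estimates CL/F and V/F from the concentration profiles and does not use the noncompartmental ke, so the wording does not reach the population model. And samples at 0, 24 and 48 h fall on three calendar days, so the 3-day statement may agree with the schedule; the article should say so.

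**Conclusion.** The ke definition is wrong as written and should be corrected. Its invalidity follows from units alone and needs no assumption about half-life or window. The 93 h against 9.3 h example illustrates the size under the assumed decline. The correction matters for the noncompartmental half-life, AUC to infinity and volume, since the study seeks differences between constitutions in the rate and extent of metabolism.

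The window is a risk for FOR and 5-O-M only if their human half-lives resemble the rat means. On the rat figures the extrapolated share is 47% and 51% at the unstated last time, or about 29% to 35% at 48 h if that time was 12 or 24 h. On the same figures ONO and AST-IV are adequately covered. This is enough to justify a rule for heavily extrapolated analytes, but not to call the schedule inadequate.

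**What to change.** - State that ke is minus the least-squares slope of ln(concentration) on time, over at least three terminal points after Cmax.
- State that for any analyte whose extrapolated share of AUC to infinity is large (for example above 20%), constitutions are compared on AUC to a common last time instead. Apply the rule by analyte, in the same way to all three constitution cohorts.
- Reconcile the 3-day blood and urine statement in Drug administration with the 48 h in Sample collection and Analytical assays: say whether three calendar days or 72 h is meant.

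The cost is a few sentences. No extra sample or assay is needed, because AUC to a common time uses data already collected. Later samples and a log-down trapezoid are optional. The yield of later samples is unproven: no quantitation limit is given, and the rat Cmax of 5-O-M was only 0.14 ng/ml.

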### Deep phenotyping with genomics and functional genomics approaches

Within pharmacokinetics of the Qishe pill, standardized workflows for the omics characterization of biosamples will be developed. Currently, genomic variants will be analyzed for 144 subjects with the aid of the Human- CoreExome + v1.1-Psych Array. For a subset of 144 subjects, whole blood expression data will be generated using Illumina’s HT-12 bead chips. The findings will be complemented with proteomic and metabolomic data using established workflows. Cytochrome P450 genes, such as CYP1A1, CYP1A2, CYP2D6, CYP2C9, CYP2C19, CYP2E1, CYP3A4 and CYP3A5, among other, will be the targets.

Metabolomics provide comprehensive snapshots of the metabolome of body fluids such as plasma or urine. High-throughput metabolomic analyses mainly based on 1H nuclear magnetic resonance (NMR) spectroscopy, a nondestructive analysis with minimal preparation requirements, will be performed. NMR spectroscopy provides robust and reproducible measurements. Mass spectrometry (MS) with high analytical sensitivity will be used for additional detailed studies.

Integrated analyses of these data for associations with clinical and subclinical phenotypes will be performed using the bioinformatics groups of the *TCM* constitutional type classification.

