**Methods/Design:**

Healthy subjects (N = 108) selected based on constitutional types will be assessed, and standardized pharmacokinetic protocol will be used for assessing demographic, physiological, and pathological data. Laboratory biomarkers will be evaluated and blood samples collected for pharmacokinetics(PK) analysis and second-generation gene sequencing. In single-dose administrations, subjects in each constitutional type cohort (N = 36) will be randomly divided into three groups to receive different Qishe pill doses (3.75, 7.5 and 15 grams).

Multiomics, including next generation sequencing, metabolomics, and proteomics, will complement the Qishe pill’s multilevel assessment, with cytochrome P450 genes as targets. In a comparison with the general population, a systematic population pharmacokinetic (PopPK) model for the Qishe pill will be established and verified.

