## Methods/Design

### Study design

This single-center, three cohort, open-label, double-Latin-sequence, crossover study will be conducted in 108 healthy adult subjects (36 subjects in each cohort) who meet the inclusion and exclusion criteria. The experiments will be conducted in accordance with good clinical practice procedures, all applicable regulatory requirements, and the guiding principles of the Declaration of Helsinki. This study was approved by the ethics committee of the institutional review board in Longhua Hospital, Shanghai University of TCM (2013-LCSY-064). After completing baseline description of the study to the enrolled subjects, written informed consent will be obtained from each of them.

The sample size was established according to GCP guidelines of SFDA, which recommend 8 to 12 subjects in a clinical pharmacokinetic trial. The study will take place at the phase I unit of Longhua Hospital, Shanghai University of TCM from Nov. 2014 to Dec 2016.

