### Highlights

Diagnosis and treatment based on an overall analysis of the illness and patient’s condition is the essence of the *TCM* theory. Rational medication is dependent upon a basic understanding of the way patients handle drugs (pharmacokinetics) and their response to specific drug effects (pharmacodynamics). Moreover, *TCM* constitutional types in traditional Chinese recipes could significantly influence the plasma concentration-time and their pharmacokinetic parameters after oral administration [38,39]. As data collection and OMICS analyses in PopPK of the Qishe pill will be processed simultaneously, research is focusing on the analyses of PK, OMICS and laboratory data to generate new hypotheses for translational research such as individualized dose, individualized scope of *TCM* and trial simulation.

The present study will establish three cohorts to detect potential differences in pharmacokinetic characteristics of the Qishe pill constituents in the three different *TCM* constitutional types, to assess whether the rate and extent of drug metabolism will be altered in *Qi-*deficiency or *Blood*-stasis constitutional types. If the differences in the Qishe Pill pharmacokinetics among the three major constitutional groups were known, personalized medication strategies for people with the three major constitutional types could be provided for the application of TCM.

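### The stated genomic sample of 144 exceeds the 108 subjects enrolled, the general-population comparison has no described comparator, and the listed specimens do not match the DNA and whole-blood RNA assays

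*Protocol article*

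**What the plan says.** The Study design section describes a three-cohort trial: "crossover study will be conducted in 108 healthy adult subjects (36 subjects in each cohort) who meet the inclusion and exclusion criteria". The abstract gives the same total, and the section on inclusion and exclusion criteria lists three cohorts of 36 by constitutional type. Table 3 requires each subject to be typed as one of those three.

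The section on deep phenotyping gives a different number: "Currently, genomic variants will be analyzed for 144 subjects", using a genotyping array. It continues: "For a subset of 144 subjects, whole blood expression data will be generated using Illumina’s HT-12 bead chips".

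The abstract adds an aim that reaches beyond the three cohorts: "In a comparison with the general population, a systematic population pharmacokinetic (PopPK) model for the Qishe pill will be established and verified".

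On specimens, the Sample collection section says: "For the PK analysis and second-generation gene sequencing, 5 ml blood samples will be collected into tubes containing ammonium heparinate". Those tubes are centrifuged at once to give plasma, which is stored frozen. The further stored materials named there are EDTA-plasma, serum and urine.

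**The concern.** A trial cannot genotype more of its own subjects than it enrols. If 144 is an error, the genomic part of the plan overstates its sample size, and any reader judging the precision of the genotype work starts from the wrong number. If 144 is intended, 36 people are to be genotyped whose recruitment, eligibility, consent and dosing the article does not describe.

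The comparison with the general population raises a similar question. The balanced type (Gentleness in Table 1) is not among the types admitted, so no enrolled group represents people outside the three selected types. Without a named comparator, the data support contrasts among those three types only.

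The specimen list bears on whether the assays can run on what is kept. Germline genotyping normally uses DNA from nucleated blood cells, and whole-blood expression needs RNA from whole blood. Plasma is what remains once the cells have been removed. The Trial status section says recruitment and prescreening began in December 2014. If cells are being discarded, a later change of wording will not recover them for subjects already sampled.

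**Working it through.** **Inputs, all from the protocol article**

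- Enrolled total: 108 (Abstract; Study design).
- Cohorts: 3, each of 36 (Study design; Inclusion and exclusion criteria).
- Dose groups per cohort: 3 (Drug administration).
- Guideline basis for the sample size: 8 to 12 subjects (Study design).
- Subjects for array genotyping: 144 (Deep phenotyping).
- Subjects for expression: a subset described with the same figure of 144 (Deep phenotyping).

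**Step 1. Reproduce the enrolled total.** Cohorts × size = 3 × 36 = 108. If the dose groups are equal, cohorts × dose groups × 12 = 3 × 3 × 12 = 108, which is the upper end of the guideline range (the lower end would give 9 × 8 = 72). The figure of 108 is internally consistent.

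**Step 2. Compare the genomic number.** 144 − 108 = 36. As a share of enrolment, 36/108 = 33%. As a share of the stated genomic set, 36/144 = 25%.

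**Step 3. Look for a stated source of 144.**

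- One more cohort of the same size: 4 × 36 = 144. No fourth cohort is described.
- A dropout allowance: 108/(1 − 0.25) = 144. No dropout rate is stated. Such an allowance would also raise the number enrolled; it would not let the number genotyped exceed the number enrolled.
- The pre-trial: the Discussion gives n = 6, and 108 + 6 = 114, which falls short of 144.

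None of these is a source that the article gives.

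**Step 4. The expression subset.** The phrase can mean part of a set of 144, in which case the size of the subset is not given. It can also mean a subset numbering 144, in which case it exceeds enrolment by 36 and is as large as the whole genotyped set. Neither reading gives a usable number.

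**Step 5. The comparator.** Enrolled subjects outside the three types: 0, by Table 3. External data sets named: 0. The Trial status section mentions blank control serum, but its stated purpose is standardising methods. It is not described as pharmacokinetic data from dosed reference subjects.

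**Step 6. Specimens against assays.**

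| Assay | What it needs | What is named |
|---|---|---|
| Gene sequencing | DNA, normally from cells | Heparin tube, centrifuged to plasma |
| Array genotyping | DNA, normally from cells | No specimen stated for the array |
| Whole-blood expression | RNA from whole blood | No whole-blood or RNA specimen named |
| Proteomics, metabolomics | Plasma, serum or urine | EDTA-plasma, serum, urine |

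The named materials suit the last row and not the first three.

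**The case against.** The strongest reply is that most of this shows incomplete description, not impossibility. A good part of that stands.

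- **Delivery.** A reader might infer that neither the genomics nor the general-population comparison can be done. The documents do not show this. Whole blood is drawn before it is spun, nothing says the cells are thrown away, and the list of stored materials is open-ended. An external data set could supply the comparator. Aliquot handling often sits in a laboratory manual. Even so, the article does more than leave this out: it assigns the sequencing blood to a tube and a processing step that ends in plasma.
- **Highlights section.** That section asks "whether the rate and extent of drug metabolism will be altered in" two of the three types. A reader might take this as a claim of departure from normal. In full, the sentence is about differences among the three types, and the one after it says so again. It can be read with the third type as reference, so only the abstract's phrase promises an outside comparison.
- **Covariates.** A reader might infer that cytochrome P450 genotypes are planned covariates in the population model and would be lost. The section on medical informatics names no covariates, and Figure 2 is not shown. These genes are described as targets of the omics work.
- **Platform.** Sequencing in the abstract and an array in the later section can both be intended, so this is no contradiction.
- **Origin of 144.** A dropped fourth cohort fits the arithmetic, but so does a 25% dropout allowance. Both are guesses.
- **Weight.** The omics work complements the pharmacokinetic study. The 144 changes no pharmacokinetic enrolment, dose allocation or sampling.

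None of these points reconciles 144 with 108.

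**Conclusion.** The concern holds in a limited form, with three parts.

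1. The genomic sample size is wrong as written. It exceeds enrolment by 36 subjects (33% of 108), and the expression subset has no usable size. This rests only on the article's own figures.
2. The comparison with the general population is unsupported as written. No comparator is enrolled and no external source is described. The enrolled cohorts support contrasts among the three types only.
3. The named specimens do not match the named genomic assays. This assumes that germline genotyping and whole-blood expression use cellular DNA and whole-blood RNA in the ordinary way. How many subjects would be affected depends on whether cells are in fact kept, which the article does not say.

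The first part is a plain contradiction. The other two are badly fixed statements that need correcting and do not prove that the work cannot be done. The pharmacokinetic sample size of 108 is unaffected.

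**What to change.** - **Genomic number.** Restate it as at most 108, or say where the additional 36 subjects come from and how they were selected.
- **Expression subset.** Give it as a number no larger than the genomic number, and say how the subset is chosen.
- **Comparator.** Either name the external data set for the general-population comparison or delete the phrase from the abstract. If it is deleted, limit conclusions to contrasts among the three constitutional types.
- **Specimens.** Amend the Sample collection section to retain the cell fraction or a whole-blood aliquot for DNA, and an RNA-stabilised whole-blood aliquot from subjects in the expression subset. Confirm what has been kept from anyone already sampled.

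The cost is a smaller stated genomic number, a narrower claim if the outside comparison is dropped, and one or two extra stored aliquots per subject (at most 2 × 108 = 216 in all). Enrolment, randomisation and the pharmacokinetic analysis need no change.
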